### 2.11. Data Analysis

Statistical analyses will be conducted using SPSS 20.00 for Windows. Descriptive statistics will be utilised to determine the demographic and clinical characteristics of participants in both groups (unpaired *t*-tests and χ^2^ tests). 

The normality and homogeneity of variance of all outcome measures will be assessed using the Shapiro–Wilk and Levene tests, respectively. If the assumptions of normality are met, a t-test will be employed, otherwise, the Mann–Whitney U test will be used to determine differences between the FtF and TR groups. Additionally, if the assumptions of normality are fulfilled, a repeated measures analysis of variance (RM-ANOVA) will be employed, otherwise, Friedman’s test will be used. Post hoc pairwise comparisons will be used to determine the intervention’s effect over time for each group (FtF and TR). Cohen’s d will be used to report effect sizes for the CoP variables. To allow repeated measures analysis, missing data will be adjusted by (1) replacing with the non-missing average values for each variable/week and (2) performing multiple imputations. Both methods will be used to make sure that the results are concordant. For all analyses, a *p*-value ≤ 0.05 will be considered statistically significant. All statistical analyses will be performed using IBM-SPSS 20.0 (SPSS Inc., Armonk, NY, USA).

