## 2. Method

### 2.1. Design

This is a non-inferiority randomised, triple-blind, controlled clinical trial. Reporting follows Standard Protocol Items: Recommendations for Interventional Trials (SPIRIT [39], see Supplementary File). Figure 1 provides an overview of the trial design. 

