### 2.3. Sample Size

The sample size was determined to detect significant changes in the effects of postural balance between FtF and TR groups after six weeks that are clinically relevant. Our proposed difference of equal to or greater than 1.5 units is based on data from previous studies [14,15,16]. A standard deviation of 1 cm^2^, an alpha of 0.05, and 80% statistical power were also considered. A 5% attrition rate was also considered, thus it was determined that a minimum of 8 participants in each group (total sample of 16) would be required. The sample size calculation was performed using GRANMO (Institut Municipal d’investigació Médica, Barcelona, Spain).

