### 2.6. Outcomes

The trial will use posturographic and clinical measures to assess the differences in the effects of FtF and TR groups using low-cost virtual reality interventions for postural control. Posturographic measures assess postural control by measuring the centre-of-pressure sway, including variables such as sway area, trajectories, and velocity in the medial–lateral and anterior–posterior directions [40]. These measures have been shown to be sensitive to measure changes in postural control due to training in various populations, including young adults [41], patients with post-stroke hemiparesis [42], patients with Parkinson’s disease [43], and children with CP [44,45,46,47,48]. Clinical measures will also be used to assess changes in postural performance in the elderly. Participants will be assessed at baseline, the ends of weeks 2, 4, and 6, and at weeks 8 and 10 (post-intervention follow-ups) using both posturographic and clinical measures. Additionally, demographic and clinical characteristics of the study groups will be included.

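### The TR-versus-FtF comparison is chosen by a weak normality pre-test with no baseline term named, and its rank branch specifies no difference in cm² with a confidence interval

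*Protocol article*

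**What the plan says.** The protocol article declares the aim in section 2.1: "This is a non-inferiority randomised, triple-blind, controlled clinical trial". Section 2.6 sets the visits: "Participants will be assessed at baseline, the ends of weeks 2, 4, and 6, and at weeks 8 and 10". CoP sway area, the primary outcome, is therefore available before treatment for every participant.

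Section 2.11 first applies Shapiro–Wilk and Levene tests to every outcome. For the arm comparison it then says "If the assumptions of normality are met, a t-test will be employed", with Mann–Whitney U as the alternative. As an additional analysis under the same normality condition, "a repeated measures analysis of variance (RM-ANOVA) will be employed, otherwise, Friedman’s test will be used". Post hoc comparisons are aimed at change over time within each arm. Cohen's d is to be reported for the CoP variables, with no normality condition attached.

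The section names no baseline covariate, change score, group factor or group-by-time term.

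**The concern.** A non-inferiority conclusion rests on an estimated TR minus FtF difference and its confidence interval, on a scale known in advance. Here the data choose the scale. If normality is accepted, the t-test supplies a mean difference in cm². If it is rejected, Mann–Whitney U as planned supplies a rank comparison, with no difference in cm² and no interval. Switching on a Shapiro–Wilk test in groups of 8 means switching partly by chance and often failing to switch when the data are skewed.

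Friedman's test does not repair the rank branch. It ranks visits within each participant, so it has neither a group nor a group-by-time term.

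Baseline sway area, already collected, also has no stated role in the arm comparison. With 16 participants, precision given up there is hard to recover elsewhere.

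**Working it through.** **Inputs from section 2.3.** Difference: "Our proposed difference of equal to or greater than 1.5 units is based on data from previous studies". Variability and error rates: "A standard deviation of 1 cm^2^, an alpha of 0.05, and 80% statistical power were also considered". Attrition: "A 5% attrition rate was also considered". Result: "a minimum of 8 participants in each group (total sample of 16) would be required". I take the 1.5 units to be cm² and alpha to be two-sided; the section states neither.

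**Input not in the documents.** The correlation r between baseline and week-6 sway area. I show r from 0 to 0.8.

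**1. The plan's own figure.** n per arm = 2 × (1.960 + 0.842)² × 1² / 1.5² = 6.98, so 7. With 5% attrition, 7 / 0.95 = 7.4, so 8. The stated 8 per arm reproduces, as an unadjusted two-sample comparison.

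**2. Unadjusted comparison at 8 per arm.** 95% CI half-width = t(0.975; 14 df) × SD × √(2/8) = 2.145 × 0.5 = 1.07 cm². Power for a difference of 1.5, from the noncentral t distribution, is 79.7%.

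**3. ANCOVA on baseline at 8 per arm.** Residual variance is (1 − r²), one degree of freedom is lost, and estimating the covariate slope inflates the variance by 1 + 1/(2 × 8 − 4) = 13/12. Half-width = t(0.975; 13 df) × √[(1 − r²) × (2/8) × 13/12]. For r = 0.6: 2.160 × √(0.64 × 0.25 × 1.0833) = 2.160 × 0.416 = 0.90 cm².

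| Analysis | Half-width (cm²) | Power for 1.5 |
|---|---|---|
| Unadjusted t-test | 1.07 | 79.7% |
| ANCOVA, r = 0 | 1.12 | 75.9% |
| ANCOVA, r = 0.3 | 1.07 | 79.7% |
| ANCOVA, r = 0.4 | 1.03 | 82.8% |
| ANCOVA, r = 0.6 | 0.90 | 91.4% |
| ANCOVA, r = 0.8 | 0.67 | 99.3% |

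Break-even lies near r = 0.3.

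**4. How the pre-test behaves.** Assume it is run in each arm of 8 at the 5% level, with a switch if either arm rejects.
- Truly normal data: chance of a switch = 1 − 0.95² = 9.75%. Simulation (8,000 trials per setting) gave about 10%.
- Log-normal data with log-scale SD 0.5: rejection in about 19.6% of arms, so a switch in 1 − 0.804² = 35% of trials. The skew goes unnoticed about two times in three.
- Type I error of the whole two-stage procedure, under normal data and a somewhat more skewed log-normal: 0.049 to 0.054.

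**5. Friedman's test.** In simulated data for 16 participants and 6 visits, adding 1.5 to every value in one arm left the statistic unchanged (4.93, p = 0.42 both times). It carries no information on a difference in level between arms.

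**The case against.** The strongest reply is that the plan does compare the arms in both branches and that the tests are valid. Much of this stands.

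- **Friedman's test.** A reader might infer that a failed normality test leaves the arms uncompared. Section 2.11 does not support that. Friedman's test replaces only the additional over-time analysis, and Mann–Whitney U still compares FtF with TR. As a within-arm description of change, Friedman's test is legitimate.
- **Estimate of the difference.** A reader might infer that the trial could end with no estimate of TR minus FtF. That overlooks the mean difference in the t-test branch and the Cohen's d planned regardless of normality. The gap is narrower: the rank branch has no difference in cm² with an interval.
- **Error rate.** A reader might expect the pre-test to inflate type I error. The simulation shows no material inflation.
- **Baseline.** The article does not say whether the t-test uses week-6 values or changes from baseline, nor to which of these the SD of 1 cm² refers. If that SD is for raw values and change scores were intended, the half-width is 1.07 × √[2(1 − r)]: 1.17, 0.96 and 0.68 cm² at r = 0.4, 0.6 and 0.8, against 1.03, 0.90 and 0.67 for ANCOVA. Most of the gain is then already captured at high correlations, but not at low ones. If the SD already refers to change, the table above does not apply directly.
- **Chance imbalance.** With 8 per arm, the standard error of a baseline difference is √(2/8) = 0.5 SD, so a gap above 0.5 SD arises in 32% of randomisations. The randomised test already allows for this in its error rate, so it is a matter of precision and not of bias.

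It does not help to leave the matter to a separate analysis plan: the article itself fixes the choice of test.

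**Conclusion.** The concern holds as a weakness in how the primary comparison is fixed, not as an invalid test. Two parts need no assumption about correlation. The scale of the arm comparison depends on a pre-test with little power at 8 per arm, and the rank branch specifies no TR minus FtF difference in cm² with a confidence interval, which Friedman's test cannot supply either.

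The precision part is conditional. If the SD of 1 cm² refers to raw week-6 values and these are compared without adjustment, the half-width falls from 1.07 to 0.90 cm² and power for the stated 1.5 difference rises from 79.7% to 91.4% at r = 0.6. The gain is nil near r = 0.3 and becomes a small loss at r = 0 (1.12 cm², 75.9%). The documents do not give r, so confidence in the size is limited. I quote power only at 1.5, the one difference the article states. The change is worth making before unblinding; it is not a reason to doubt that the planned tests hold their error rate.

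**What to change.** Name one primary analysis, to be used whatever the normality test shows: ANCOVA of week-6 CoP area on arm and baseline CoP area. Fix the scale in advance, for example the log scale if skew is expected, with any margin expressed on that same scale. Report the adjusted TR minus FtF difference with its 95% CI.

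Use a permutation test or rank-based ANCOVA as the robustness check. Drop the normality-gated switch for the arm comparison, and keep Friedman's test for describing change within each arm only. A larger mixed model with visit and centre terms would be heavy for 16 participants and is not needed for this purpose.

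Cost: revised analysis wording, one degree of freedom, and the small loss of precision shown above if the correlation proves low. No new data or visits are required.

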## Abstract

**Background:** Several exercise methods with virtual reality devices have been used in treatments for older adults and patients with neurodegenerative diseases, although the mechanisms continue to be elucidated. The aim of this study is to establish the feasibility and effectiveness of a rehabilitation programme using low-cost virtual reality aimed at improving postural balance in older adults. It also seeks to compare low-cost virtual reality under two delivery modalities, telerehabilitation (TR) in elderly centres and face-to-face (FtF) in rehabilitation centres. **Methods:** The study is set up as a non-inferiority two-arm parallel triple-blind randomised controlled clinical trial. Sixteen persons aged 65 to 75-years-old will be included. Eighteen Wii therapy sessions (25–30 min) will be provided through both FtF (control group, *n* = 8) and TR (exposure group, *n* = 8), both with a Nintendo Wii balance board. Data will be collected at baseline (week 0), during the Wii therapy sessions (weeks 2, 4, and 6), and during the follow-up (weeks 8 and 10). The primary outcome will be the area of centre-of-pressure (CoP) sway; secondary outcomes will be medial–lateral and anterior–posterior velocity and standard deviation of CoP; and tertiary outcomes will be clinical measures: single-leg stand, timed up-and-go tests, Barthel Index, and Tinetti’s scale. Statistical analyses will be performed using SPSS 20.00 for Windows. The trial adheres to the Declaration of Helsinki and the Chilean laws of rights and duties of the patient and research in humans. Ethical approval was obtained from the Ethics Committee of the University of Talca. Written informed consent will be obtained from participants. **Discussion:** In this trial, older adults from a Chilean city with a large rural and underserved population share will be included to test the feasibility and effectiveness of a rehabilitation programme using low-cost VR aimed at improving postural balance to generate evidence to support decision makers generating public health policy. **Trial registration:** Australian New Zeeland Clinical Trials Registration (ACTRN12621001380886).

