## 3. Discussion

Anticipated findings from this trial suggest that the TR modality will exhibit non-inferior effectiveness to the FtF modality, as evaluated through clinical and posturographic assessments. This expectation draws support from preliminary evidence surrounding the implementation of TR and VR interventions in different settings. According to a recent systematic review, telemonitoring and telerehabilitation were the most used methods of telecare interventions in older populations. The findings from various studies indicated that these interventions had a positive impact on different dimensions of quality of life, particularly in older adults. Evaluating the impact of telecare interventions can provide valuable insights for system developers to improve the effectiveness of current and future telecare technologies to better meet the needs of users, particularly older adults. Future research can focus on evaluating the impact of specific telecare systems on targeted populations using diverse research methodologies. This can help in understanding the effectiveness of telecare interventions in different settings and for different populations and guide the development and implementation of telecare technologies that are tailored to specific user requirements [51]. Similarly, telehealth occupational therapy has been widely utilised for older adults, with a focus on providing convenient occupational assessment and intervention for both occupational therapists and their elderly clients. Telehealth occupational therapy also allows for monitoring of patients’ activities and provides rehabilitation counselling and health education to older adults and their caregivers, resulting in improved home life security and efficacy of occupational therapy interventions. Particularly during the COVID-19 pandemic, telehealth has emerged as a valuable alternative to face-to-face modalities, ensuring continuity of care while minimizing risks of infection [52].

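### The trial is declared non-inferiority, but it is sized and analysed only for a difference and states no margin, so the planned analysis cannot test the declared hypothesis

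*Protocol article*

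**What the plan says.** **Declared design.** Section 2.1 states: "This is a non-inferiority randomised, triple-blind, controlled clinical trial". The Abstract says the same: "The study is set up as a non-inferiority two-arm parallel triple-blind randomised controlled clinical trial".

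**Expected conclusion.** The Discussion (section 3) anticipates that "the TR modality will exhibit non-inferior effectiveness to the FtF modality".

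**Sample size (section 2.3).** The aim is framed as detection: "The sample size was determined to detect significant changes in the effects of postural balance between FtF and TR groups after six weeks". The effect is given as follows: "Our proposed difference of equal to or greater than 1.5 units is based on data from previous studies". The remaining inputs are: "A standard deviation of 1 cm^2^, an alpha of 0.05, and 80% statistical power were also considered". After 5% attrition the result is 8 per group, 16 in total. The sidedness of alpha is not given.

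**Analysis (section 2.11).** A t-test, or a Mann–Whitney U test if normality fails, "will be used to determine differences between the FtF and TR groups". Repeated measures ANOVA or Friedman's test and post hoc pairwise comparisons are also planned, and Cohen's d is reported for the centre-of-pressure (CoP) variables. One significance threshold, p ≤ 0.05, covers all analyses.

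**Direction.** Section 2.6.1 makes CoP sway area the primary outcome and says that higher values mean poorer balance control.

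No section states a non-inferiority margin or compares an estimate or confidence limit with one.

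**The concern.** A non-inferiority trial tests the null hypothesis that the new modality is worse than the comparator by at least a stated margin. Section 2.11 tests a different null, that the groups do not differ. Rejecting it shows a difference; failing to reject it shows nothing about a margin. The article therefore names one hypothesis and supplies the sizing and test for another.

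The results are meant to inform public health policy on remote delivery. With 16 participants a non-significant difference is likely even when TR is appreciably worse, and the article contains no criterion that would stop such a result being offered as support for the conclusion its Discussion expects. The smaller and noisier the trial, the more easily that would happen.

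**Working it through.** **Inputs.** Difference 1.5 units, SD 1 cm², alpha 0.05, power 80%, attrition 5%, 8 per arm (section 2.3); 1:1 allocation (section 2.8). Two assumptions are needed: the 1.5 units are cm² of CoP area, since the SD is in cm², and alpha is two-sided.

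**1. Reproducing the stated sample size.** For a two-sided comparison of two means:

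n = 2(z₀.₉₇₅ + z₀.₈₀)² × SD² / Δ² = 2(1.960 + 0.842)² × 1 / 1.5² = 6.98, so 7 per arm. With attrition: 7 / 0.95 = 7.4, so 8 per arm and 16 in total.

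This matches the plan exactly. A non-inferiority calculation with margin 1.5, true difference 0 and one-sided alpha 0.025 has the same formula and gives the same 8 per arm. The number alone therefore does not show which was intended; the wording of section 2.3 points to a difference to be detected.

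**2. Chance of p > 0.05 when TR is truly worse by δ.** For the two-sided t-test with n per arm, df = 2n − 2 and the noncentrality is δ / (SD × √(2/n)). With n = 8, √(2/8) = 0.5, so δ = 1.5 gives noncentrality 3.0 against a critical value of 2.145. With n = 7, √(2/7) = 0.535 and the critical value is 2.179.

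| True deficit of TR (cm²) | 8 per arm | 7 per arm |
|---|---|---|
| 1.5 (the plan's own difference) | 20% | 27% |
| 1.0 (assumed) | 54% | 59% |
| 0.75 (assumed) | 71% | 75% |

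The second and third rows are rates of a false non-inferiority claim only if the margin is at or below 1.0 or 0.75 cm² respectively.

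**3. Precision.** The 95% CI half-width is 2.145 × 0.5 = 1.07 cm² with 8 per arm and 2.179 × 0.535 = 1.16 cm² with 7. With 8 per arm and an observed SD of 1, a just non-significant estimate near +1.07 would have an upper limit near 1.07 + 1.07 = 2.1 cm², beyond the 1.5 cm² that the plan calls clinically relevant.

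**4. Power of a real non-inferiority test.** With 8 per arm, SD 1 and true difference 0, power is the upper tail of the noncentral t distribution (df 14) with noncentrality margin / 0.5. The critical value is 2.145 at one-sided 0.025. The last column applies the formula in step 1 with the margin in place of Δ (one-sided 0.025, 80% power) and 5% attrition.

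| Assumed margin (cm²) | Power, one-sided 0.025 | Power, one-sided 0.05 | Total N for 80% power |
|---|---|---|---|
| 1.5 | 80% | 89% | 16 |
| 1.0 | 46% | 60% | 34 |
| 0.75 | 29% | 41% | 60 |
| 0.5 | 15% | 24% | 134 |

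**The case against.** **The article never says that a non-significant p-value means non-inferiority.** This is correct. A reader might infer that it will be read that way, because section 2.11 offers no other route to the conclusion expected in the Discussion. But section 2.11 only says what counts as significant, and the Discussion states an expectation, not a decision rule. The inference therefore stays conditional. What does not depend on it is that the declared hypothesis has no test.

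**The 1.5 units may be an unlabelled margin.** The arithmetic allows this, since both calculations give 8 per arm. Section 2.3, however, presents it as a difference to detect and calls it clinically relevant. As a margin it would equal 1.5 SD and would tolerate a deficit up to the size the article itself calls relevant. Section 2.11 would still not use it.

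**An unseen analysis plan may hold the confidence-interval rule.** Its absence from a condensed article would not by itself be a finding. The point rests on what the article does state: a non-inferiority design beside a difference-based sample size and difference tests.

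**Other procedures are planned.** Repeated measures ANOVA and Cohen's d are listed, so the t-test or Mann–Whitney test is not the whole analysis. Neither compares anything with a margin.

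**The direction is not missing.** Section 2.6.1 says that higher sway area is worse, and the Discussion says which arm is to be non-inferior to which.

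**Conclusion.** The point stands: the declared design and expected conclusion are non-inferiority, while the sample size and the stated tests address a difference and no margin is given. The analysis as written cannot test the declared hypothesis.

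The figure that rests on the plan's own values is the 20% chance of a non-significant result with 8 per arm (27% with 7) when TR is truly worse by 1.5 cm². It becomes a false-claim rate only if non-significance is taken as support for non-inferiority. For comparison, a non-inferiority test errs at its margin in 2.5% of trials, or 5% if the unstated sidedness of alpha means one-sided 0.05. It would be tempting to quote 54% and 71% as the trial's false-positive rate. The article does not support that, because it states no margin: if the margin were 1.5 cm², a deficit of 1.0 or 0.75 cm² would be truly non-inferior.

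All figures assume an SD of 1 cm², normal outcomes and a two-sided 0.05 t-test.

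**What to change.** Choose one of two routes.

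(a) **Keep non-inferiority.** Make the primary analysis the TR minus FtF difference in CoP area at week 6 with a two-sided 95% CI. Conclude non-inferiority only if the upper limit lies below a margin in cm² that is fixed and justified before unblinding. Say explicitly whether the 1.5 units is that margin and, if so, why a deficit of the size called clinically relevant is acceptable. Restate the power, and if necessary the sample size, for the margin chosen.

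(b) **Drop the label.** If no defensible margin suits 16 participants, delete non-inferiority from the Abstract, section 2.1 and the Discussion, and report a feasibility and estimation study with confidence intervals. This fits the feasibility aim already stated in the Background.

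In either case, state that p > 0.05 is not evidence of non-inferiority.

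**Cost.** Route (b) is a change of wording, but it gives up the non-inferiority claim. Route (a) is a change of wording only if 1.5 cm² is defended as the margin. For any margin clearly below that, the trial at 16 participants is likely to be inconclusive on non-inferiority, and keeping 80% power would need, for example, 34 participants for a margin of 1.0 cm² or 60 for 0.75 cm².

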### 2.8. Allocation

Participants will be randomly assigned to either the control (FtF) or experimental group (TR) with 1:1 allocation as per a computer-generated randomization schedule stratified by site and the baseline score of the Action Arm Research Test using permuted blocks of random sizes. For concealing treatment allocation, the block sizes utilised in this study will not be divulged. This statistical approach, tailored to the randomised and block design, has been adopted to ensure the practicality and cost-effectiveness of conducting the clinical trial.

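### Replacing missing values by the variable/week average biases the arm difference or understates its standard error, and agreement with multiple imputation does not repair this

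*Protocol article*

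**What the plan says.** Section 2.11 (Data Analysis) says that, so that repeated-measures analysis can be run, "missing data will be adjusted by (1) replacing with the non-missing average values for each variable/week and (2) performing multiple imputations". It adds: "Both methods will be used to make sure that the results are concordant". Neither method is named as primary, and nothing is said about what follows if they disagree. The average is indexed by variable and week; arm is not mentioned.

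Section 2.1 sets the framework: "This is a non-inferiority randomised, triple-blind, controlled clinical trial". The analyses described in section 2.11 are tests of difference (t-test or Mann–Whitney, RM-ANOVA or Friedman) at a p-value threshold of 0.05.

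Section 2.3 gives the sizes that matter here: "A 5% attrition rate was also considered", and "a minimum of 8 participants in each group (total sample of 16) would be required". Section 2.6 lists six assessments, from baseline to week 10.

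**The concern.** A mean put in place of a missing value adds no spread, yet it is counted as an observed participant. The reported variance falls and the degrees of freedom are overstated. If the mean comes from both arms together, each filled value also moves its arm toward the other.

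In a small trial this shows quickly. With 8 per arm, one missing participant is 1/8 = 12.5% of the arm. The concordance check is no safeguard. Agreement with a method that has a known error confirms nothing, and disagreement leaves a choice between two results after the data are seen.

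**Working it through.** **Inputs.** 8 per arm with 1:1 allocation, SD 1 cm², difference 1.5 (read as cm²), alpha 0.05, power 80%, attrition 5% (sections 2.3 and 2.8). Assumptions added here: normal outcomes, values missing completely at random, a pooled-variance t analysis at one visit, and two-sided alpha.

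**The plan's own figure.** n = 2(1.960 + 0.842)² × 1² / 1.5² = 6.98, so 7 per arm. Allowing for attrition, 7 / 0.95 = 7.4, so 8 per arm. The stated size reproduces. Planned attrition is 0.05 × 16 = 0.8, or about 1 participant of 16.

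**Reading A: average over both arms.** Take true means of 1.5 (TR) and 0 (FtF).

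- 1 TR value missing: the fill is 7 × 1.5 / 15 = 0.70. The TR mean becomes (7 × 1.5 + 0.70) / 8 = 1.40, and the difference is 1.40.
- 1 missing per arm: the fill is 0.75. The arm means become 11.25 / 8 = 1.406 and 0.75 / 8 = 0.094, and the difference is 1.31.
- 2 missing per arm: the difference is 1.5 × 6/8 = 1.125, or 1.13.

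**Reading B: average within arm.** The difference stays at 1.50. With a and b values observed in the two arms, the true SD of the difference is √(1/a + 1/b). The filled data report a pooled variance that is (a + b − 2)/14 of the observed-data one, and treat it as coming from 8 + 8 values. The reported SE is therefore about √[(a + b − 2)/14 × 2/8]. The filled test uses the critical value t(0.975, 14 df) = 2.145. Dividing that by the ratio of true to reported gives the cut-off that is really applied to a valid t statistic on a + b − 2 df.

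| Missing | True SD | Reported SE | Ratio | Effective cut-off (df) | Two-sided type I error |
|---|---|---|---|---|---|
| 1 of 16 | 0.518 | 0.482 | 1.074 | 1.997 (13) | 6.7% |
| 1 per arm | 0.535 | 0.463 | 1.155 | 1.857 (12) | 8.8% |
| 2 per arm | 0.577 | 0.423 | 1.366 | 1.570 (10) | 14.8% |

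The reported SE in the table is the square root of the expected variance. The mean SE over 200,000 simulated trials with one missing per arm is slightly lower, 0.453, against a true 0.535.

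**Illustrative non-inferiority test.** Suppose that the upper limit of a 95% interval is compared with a margin of 1.5, and that the true difference equals the margin. The nominal error is 2.5%. Reading B gives half the two-sided errors above. Reading A was simulated.

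| Missing | Observed cases | Reading B | Reading A |
|---|---|---|---|
| 1 of 16 | 2.5% | 3.4% | 3.9% |
| 1 per arm | 2.4% | 4.4% | 5.8% |
| 2 per arm | 2.5% | 7.4% | 12.6% |

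**The test of difference that the article describes, one missing per arm.**

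| | Observed cases | Reading A | Reading B |
|---|---|---|---|
| Type I error, true difference 0 | 5.0% | 5.0% | 8.8% |
| Chance of significance, true difference 1.5 | 73% | 73% | 82% |

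**Repeated-measures check.** A group-by-time RM-ANOVA was simulated with six visits, equal correlation of 0.3 to 0.7 (assumed), and dropouts missing the last three visits. At nominal 5%, reading B gives about 8.4 to 8.7% with one dropout per arm and 13.4 to 14.0% with two. Reading A stays near 5%.

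**The case against.** A reader might infer that mean replacement is the only method, that it pulls the arms together, and that dropouts therefore favour a non-inferiority claim. The documents do not support that as a flat statement, for three reasons.

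- Multiple imputation is planned alongside.
- Shrinkage needs the average to be taken over both arms. The literal index leaves arm out, but the text does not say that the arms are pooled.
- A gain for non-inferiority needs an interval compared with a margin. Section 2.11 describes only tests of difference, and section 2.3 uses 1.5 as a difference to detect. Under the described test, within-arm filling produces too many significant differences, which works against a non-inferiority claim. Pooled filling leaves that test close to nominal.

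Three further objections are fair.

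- Section 2.11 ties the filling to the repeated-measures analysis, so the two-sample comparison might use observed data only. The illustrative RM-ANOVA shows that the within-arm problem remains there.
- At about the planned attrition the inflation is modest: 3.4 to 3.9% against 2.5% on the assumed margin test.
- Naming a primary method, or stating how arm enters, could be left to an analysis plan that is not shown.

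The last point does not rescue mean replacement itself. The article specifies it, and it fails on either reading.

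**Conclusion.** The concern holds in a limited form. Section 2.11 gives single mean replacement equal standing with multiple imputation, guarded only by a concordance check. Depending on how the average is formed, the result is either a shrunken arm difference (1.40, 1.31 or 1.13 in place of 1.5) or a standard error that is too small (type I error of about 6.7%, 8.8% or 14.8%).

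The direction of harm depends on the reading and on the test. On an interval-versus-margin test both readings are anti-conservative; on the stated test of difference, within-arm filling yields false differences.

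These sizes rest on SD 1, normal data and values missing completely at random. The non-inferiority figures also rest on an assumed margin of 1.5 and a one-sided 2.5% level. The effect is small at 1 of 16 missing and grows quickly beyond that. The rule should be changed, but the finding does not undermine the design.

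**What to change.** 1. Delete mean replacement and the concordance check.
2. Name as primary a likelihood-based mixed model on all observed visits, which SPSS provides. It needs no filled values to handle repeated measures. With 16 participants, keep the covariance structure simple: an unstructured one over six visits has 6 × 7 / 2 = 21 parameters.
3. Keep multiple imputation as a sensitivity analysis, with arm in a small imputation model: arm, baseline and an adjacent visit. Do not fit it separately by arm on all other visits. Week 6 on the five other visits needs 6 parameters from 7 or 6 observed participants, leaving 1 or 0 residual degrees of freedom. The small joint model has 4 parameters on 14 or 12 observed participants, leaving 10 or 8.
4. Add one sensitivity analysis that shifts missing TR values in the unfavourable direction, which is upward because a larger sway area is worse (section 2.6.1).

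The mixed model would replace the RM-ANOVA now planned, so the change should be recorded as an amendment to the analysis before group data are examined. The cost is analysis-plan wording and a little programming, with no change to recruitment, visits or measurements.
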